## Abstract

**Introduction:**

Stroke is a leading cause of death and disability. The development of dementia after stroke is common. Vascular risk factors (VRF) which contribute to stroke risk can also contribute to cognitive decline, especially in vascular dementia (VaD). There is no established treatment for VaD, therefore strategies for prevention could have major health resource implications. This study was designed to assess whether patients with early cognitive decline after stroke/transient ischaemic attack (TIA) can be easily identified and whether target-driven VRF management can prevent progression to dementia.

**Objectives:**

The primary objective is to establish the feasibility of recruitment and retention of patients with early cognitive decline to a randomised controlled trial of enhanced VRF management. Secondary objectives include: (a) to determine the potential clinical benefit of the intervention; (b) to estimate the sample size for a future definitive multicentre randomised controlled trial; (c) to inform a future economic evaluation; (d) to explore the link between VRF control and the incidence of cognitive impairment on longitudinal follow-up in a UK population after stroke/TIA with current routine management.

**Methods:**

100 patients with cognitive decline poststroke/TIA will be recruited from stroke services at the Norfolk and Norwich University Hospital. After collection of baseline data, they will be randomised to intervention (3 monthly follow-up with enhanced management) or control (treatment as usual by the general practitioner). At 12 months outcomes (repeat cognitive testing, VRF assessment) will be assessed. A further 100 patients without cognitive decline will be recruited to a parallel observational group from the same site. At 12 months they will have repeat cognitive testing.

**Ethics and dissemination:**

Ethical approval has been granted in England. Dissemination is planned via publication in peer-reviewed medical journals and presentation at relevant conferences.

**Trial registration number:**

42688361; Pre-results.

Strengths and limitations of this studyThe protocol uses a validated cognitive screening test, which is sensitive and specific for the detection of mild cognitive impairment as well as dementia.Data will be collected on a range of vascular risk factors.The study is open-label, but repeat cognitive testing will be completed by a member of the research team who is blinded to allocation and baseline cognitive status.The chosen follow-up period of 12 months may limit our ability to detect changes in cognition.

## Introduction

### Background

Stroke is one of the leading causes of death and disability^1^ and current demographic trends suggest that the total numbers of people with a stroke will rise due to the ageing population.^2^ Cognitive decline after stroke poses a significant problem considering that up to 30% of patients may potentially develop dementia as early as 3 months after their cerebrovascular event.^3^ Stroke may unmask previously unrecognised cognitive impairment,^4 5^ or may trigger new cognitive decline due to VaD, Alzheimer’s disease or mixed pathology.^6 7^

The World Alzheimer Report emphasised the benefit of early diagnosis with future savings from delayed institutionalisation and care costs across the disease course.^8^ Similarly, the UK Government has identified the timely diagnosis of dementia in primary care as a priority.^9^ An effective strategy in preventing VaD could have major resource implications, with at least one in five dementia cases having a VaD element and dementia costing the UK economy £23 billion per year.^10^ Most importantly, ‘*how best to improve cognition after stroke’* was reported to be the highest priority research topic in a survey of patients with stroke.^11^ Identifying patients who have signs of early cognitive decline after stroke or TIA could provide a window of opportunity for saving resources and improving patient outcomes if further cognitive decline could be prevented.^6^

It is reported that dementia is common after stroke and TIA.^3 4 12 13^ Reported rates range from 7.4% up to 41.3% with the variance mostly dependent on the mix of the cohort (eg, rates are higher in secondary care cohorts and those with higher rates of recurrent stroke).^14^ Our previous work shows that the risk of developing cognitive impairment appears to be greater in people with higher numbers of VRF^4^ and other work suggests that the presence of cardiovascular risk factors increases the risk of early cognitive decline progressing to dementia.^15^ Improved control of VRF leading to enhanced secondary stroke prevention may therefore help to prevent further cognitive decline after stroke/TIA in high-risk patients with evidence of early cognitive impairment.

### Rationale for the study

Observational evidence indicates that both VaD and Alzheimer’s dementia may have risk factors in common with stroke, namely VRF such as high blood pressure (BP) and diabetes.^16 17^ Despite this, whether intervening to control these risk factors can prevent dementia remains unclear.^16 18^ First, trials of antihypertensive therapy have been inconsistent. However, they may have been limited by high rates of treatment in placebo groups, high dropout rates and short follow-up.^18^ Of note, a large trial which recruited patients with stroke/TIA (PROGRESS) did demonstrate reduced cognitive decline, but not dementia, with treatment.^16 18^ Furthermore, meta-analysis of placebo-controlled trials suggests that antihypertensive therapy reduces the risk of dementia.^19^ Second, two randomised controlled trials have assessed the use of statins and found no benefit on cognition despite reduction in cholesterol levels.^20^ Third, in the ADVANCE study intensive blood glucose control in type 2 diabetics successfully reduced microvascular complications, but did not reduce rates of dementia.^18^ Finally, whether anticoagulation for atrial fibrillation (AF) can prevent cognitive decline is, at present, not addressed by the available evidence.^16 17^ In spite of this uncertainty there is evidence, as alluded to earlier, that recurrent stroke is an important factor in poststroke dementia.^14^ Given that treating VRF is beneficial for secondary stroke prevention, it therefore remains plausible that this could also have an impact on cognitive decline poststroke and further research is justified. Evidence to support this comes from a randomised controlled trial in Germany, which demonstrated a significant reduction in the need for long-term care in older adults following an intervention involving systematic identification and evidence-based treatment of cardiovascular risk factors.^21^ Although two trials similar to ours have investigated the use of an intervention targeted at controlling VRF for preventing cognitive decline after stroke and neither demonstrated a benefit of intervention at 12 months,^22 23^ a key difference with our study is that we will be targeting patients who already have signs of cognitive impairment at baseline and therefore are at higher risk of further decline.

Routine cognitive testing using validated measures which are simple and quick, such as the Montreal Cognitive Assessment (MoCA), which are shown to be sensitive and specific in detecting vascular-related cognition can identify those who are at risk of developing decline.^24–26^ We believe therefore, that detection of early cognitive decline in stroke and TIA is feasible at the time of diagnosis in secondary care and we propose that enhanced (target driven) VRF control is clinically effective, cost-effective and safe.

The reported incidence of dementia poststroke is variable, with the highest rates being over 40%.^7 14^ Reporting differences are strongly attributable to variation in the cohorts studied.^14^ There is also some evidence to suggest that cognitive decline after TIA or minor stroke (defined as National Institute of Health Stroke Scale <3) may be transient.^27^ However, there is a lack of data based on the current UK population. This study will therefore incorporate a parallel observational arm with a view to generating relevant epidemiological data in order to provide better insight regarding cognition after stroke/TIA in this patient population.

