### Trial participants

All adult patients with confirmed stroke (first/recurrent) or TIA, identified within 8 weeks of diagnosis will be considered for the trial.

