### Identification of participants

Eligible patients will be given a detailed Patient Information Sheet (PIS) and Consent Form for consideration. After 24 hours the study team will contact the patient again and those who agree to participate will provide written informed consent and undergo a simple and validated cognitive screening test (MoCA), unless this has already been carried out by the clinical team as part of their routine care, whereupon that score can be used for study purposes. If a MoCA has been administered by the TIA clinic team the patient will be given a PIS in clinic and be followed up by phone to discuss entry into the study. Patients who have previously attended stroke services may be screened retrospectively from the Capture TIA/Stroke hospital database and followed up by phone. Those who have a MoCA score ≥26 and who verbally consent to be contacted about the study are sent a study summary sheet, a study invitation letter and consent form. If they wish to participate, the completed consent form will be returned and countersigned by a delegated member of the study team. Those who do not have a MoCA score following their stroke or TIA are invited for an appointment to give consent to take part in the study and carry out the MoCA. The patient will be enrolled into the appropriate arm of the study depending on the MoCA score.

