#### Secondary objectives

Rates of control of VRF at baseline and outcome in each group.Proportion of participants in group I achieving VRF targets at 3, 6 and 9 months for each risk factor.Difference in mean change in MoCA score between groups C and I. The between-group comparison will be based on a general linear model with group as a fixed effect and including any prognostic variables at baseline for which there is a between-group disparity. A 95% CI for the difference in means will be constructed to give an idea of the likely magnitude of benefit from the intervention.Indicative incremental cost per point gained in MoCA, DEMQOL and per QALY gained between groups C and I. Data will be analysed in terms of costs and effects for the two groups. We will analyse key drivers of costs and examine the potential of this intervention to be cost-effective.Change in MoCA score between baseline and 12 months in group O participants, and in groups O and C combined.Difference in adverse event rates between groups.Difference in mean BP between groups C and I.Difference in BP (systolic and diastolic) variability between groups C and I.Difference in PWV between groups C and I.

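### One MoCA of 20–25 admits patients whose decline may be transient, and the analysis neither reports group C on its own nor fixes index event as a covariate

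*Protocol article*

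**What the plan says.** The case for this trial, after two similar trials showed no benefit at 12 months, is that "we will be targeting patients who already have signs of cognitive impairment at baseline and therefore are at higher risk of further decline" (Rationale for the study). The same section then reports some evidence that "cognitive decline after TIA or minor stroke (defined as National Institute of Health Stroke Scale <3) may be transient", and turns to the observational arm for better insight.

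Entry works as follows:
- Stroke and TIA patients "identified within 8 weeks of diagnosis will be considered for the trial" (Trial participants). No minimum interval between event and MoCA is stated, and the Rationale holds that "detection of early cognitive decline in stroke and TIA is feasible at the time of diagnosis in secondary care".
- If the clinical team has already done a MoCA, "whereupon that score can be used for study purposes". The route "If a MoCA has been administered by the TIA clinic team the patient will be given a PIS in clinic" is also open (Identification of participants).
- A score of 20–25 leads to randomisation and a score of 26 or more leads to group O (Allocation into study arms and the sections after it).
- The next scheduled MoCA after entry is at 12 months (Ordering of assessments).

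Under Data analysis plan, Secondary objectives, the comparison is the "Difference in mean change in MoCA score between groups C and I". It comes from a general linear model that adds baseline prognostic factors only where the arms are seen to differ. The same list gives MoCA change for group O, and for O and C taken together.

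**The concern.** The trial is meant to concentrate patients at risk of further decline. If some scores of 20–25 recover without intervention, the randomised groups mix recovering and declining patients. How often that happens is something a feasibility study should pass on, because the definitive trial's eligibility rule depends on it.

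The arm the article looks to for insight cannot supply the answer, since group O contains nobody who scored 20–25. Group C can: it scored 20–25, receives usual care and is retested at 12 months. The listed analyses do not draw that out. Pooling C with O joins two groups selected on opposite sides of the cut-off. The adjustment rule also leaves index event out whenever it is balanced between the arms, even if it strongly predicts change.

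**Working it through.** The planned size (at least 50 per arm and 100 in group O) has no formal calculation behind it, so there is no stated figure to reproduce. The documents give no transient fraction, no recovery size and no SD of MoCA change. **All values below other than the group sizes are assumptions, used to show the mechanism.**

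**1. A flat mean is ambiguous.** Let a fraction f recover and gain 2 points, while the rest lose 1.
- Mean change = 2f − (1 − f) = 3f − 1.
- At f = 1/3 the mean is 0 although two thirds decline. At f = 0.3 it is −0.1.
- A group in which nobody truly changes also has mean 0. The mean alone does not separate the two cases.

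**2. Cost in precision.** Take a within-class SD of 2.5, a 3-point gap between classes and f = 0.3.
- Variance = 2.5² + 0.3 × 0.7 × 3² = 6.25 + 1.89 = 8.14, so SD = 2.85.
- 95% half-width for C–I at 50 per arm = 1.96 × SD × √(2/50). This is 1.12 points at SD 2.85 and 0.98 at SD 2.5.
- A covariate that identified the classes perfectly would therefore narrow the interval by about 0.14 points each way. Index event is only a proxy, so the real gain would be smaller.
- The same loss seen as chance imbalance: SE of the difference in recovering share = √(2 × 0.3 × 0.7/50) = 0.092, and 1.96 × 3 × 0.092 ≈ 0.54 points.

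**3. Pooling O with C.** At the target sizes the pooled mean is (100 × change in O + 50 × change in C)/150. Selection on a single score pulls retests towards the population mean: up in C and down in O. If C rose 0.6 and O fell 0.3, the pooled change would be (−30 + 30)/150 = 0. Neither movement would show.

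**4. How far a return to 26 or more can be read.** Patients were simulated as selected on one observed score of 20–25 with no true change (true SD 3, measurement-error SD 1 to 2, population mean 24 to 26).
- The mean rise at retest was 0.12 to 0.86 points.
- Between 11% and 31% scored 26 or more.

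A raw return rate therefore overstates recovery and must be labelled accordingly.

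**5. Precision of the proposed report.** For a return proportion of 0.3, the half-width is 1.96 × √(0.21/50) = 0.13 in the whole of group C. In a class of 25 it is 1.96 × √(0.21/25) = 0.18. Such figures can describe, but should not set planning inputs by themselves.

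**The case against.** Several points against the concern stand.

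- **No bias.** Randomisation gives both arms the same expected mix. The primary outcome, recruitment and retention, is not biased.
- **Entry timing is bounded.** Patients are identified within 8 weeks of diagnosis. The text of Ordering of assessments also lists a MoCA at baseline, although Table 1 marks it at screening. These may be the same test. It would be wrong to assert that persistence could never have been checked; the article simply does not require a second score.
- **The definitive sample size is not shown to be wrong.** A reader might infer that it is. With an effect of 1 point in persistent decliners only, SD 3 and 90% power at two-sided 5%, n per arm = 2 × (1.960 + 1.282)² × 9/δ². That is 190 at δ = 1 and 386 at δ = 0.7 (30% transient). But this compares two target populations. The pooled effect and SD are the right inputs for a definitive trial with the same eligibility. The dilution also assumes no benefit in recoverers, whereas the Rationale works partly through preventing recurrent stroke.
- **No contradiction.** Possible transience in some patients is compatible with higher average risk, and the article hedges the statement.

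It can also be said that subgroup splits and covariates belong in an analysis plan that is not shown. That is fair for the splits. It does not dispose of the two choices the article does fix: the rule that only unbalanced factors enter the model, and the listing of O and of O with C. The C–I analysis will yield a group C mean as a by-product, but that is the ambiguous figure of step 1 above.

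**Conclusion.** The point holds as a modest, inexpensive improvement to the analysis. Entry rests on one early MoCA, the article itself allows that decline after TIA or minor stroke may be transient, and only group C can show how often a score of 20–25 persists. The listed analyses pool group C with a group selected above the cut-off, and leave index event out of the model unless it happens to be unbalanced.

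The consequence is limited to some lost precision and to weak guidance on eligibility for the definitive trial. The size cannot be stated from the documents. Under the assumed mixture, the most that covariate adjustment could recover is about 0.14 points of half-width.

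Two stronger readings are not supported: that the C–I estimate is biased, and that the planning sample size is wrong by a known factor.

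**What to change.** In Data analysis plan, Secondary objectives, before the 12-month data are analysed:

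1. Keep the pooled C–I comparison as the main estimate. Include index event (TIA or stroke) as a prespecified covariate whether or not the arms differ on it. Add time from event to qualifying MoCA if those dates were recorded.
2. Report group C separately from group O: 12-month MoCA change and the proportion scoring 26 or more, overall and by index event. Label this exploratory, and note that part of any return to 26 or more reflects measurement error and regression to the mean.
3. Use these results descriptively to inform the definitive trial's eligibility, alongside the pooled SD and effect and not in place of them.

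A repeat MoCA before randomisation is not an option here, since recruitment closed in July 2017.

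**Cost:** analysis wording only, with no new visits or tests. The classes will be small and imprecise. The TIA/stroke split also does not isolate minor stroke, the other group the article names, because stroke severity is not among the listed baseline data.

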### Study objectives

The primary objective of the study is to determine the feasibility of randomising patients who have signs of early cognitive decline, but no dementia, into routine risk factor management or enhanced risk factor management by their GP, and to assess adherence to the proposed intervention by enrolled participants.

The secondary objectives are as follows:Determine the potential clinical benefit of enhanced control of VRF in preventing progression of cognitive decline and the development of dementia poststroke/TIA.Assess indicative cost-effectiveness of this intervention.Estimate the sample size for a future definitive multicentre randomised controlled trial.Identify any adverse events due to the intervention, including rates of recurrent stroke/TIA.Explore the incidence of cognitive impairment on longitudinal follow-up in a UK population after stroke/TIA with current routine risk factor management.

## Methods and analysis

### Study overview

This study is a single-centre, open-label parallel group study to determine the feasibility of conducting a randomised controlled trial in a National Health Service (NHS) setting on patients following stroke or TIA who have early cognitive decline. The aim is to target risk factors more intensively through enhanced monitoring and control of VRF compared with usual care. We wish to estimate the potential clinical impact and cost-effectiveness of this intervention, and the sample size for a future multicentre definitive study in an NHS setting.

There is a parallel observational study arm for patients with no evidence of cognitive decline who will have their VRF and cognitive function assessed at follow-up. The objective of the parallel observational study is to better understand the link between VRF, their control and the development of cognitive decline after a cerebrovascular event. Combining the control arm of the feasibility trial and observational cohort will provide further information on these links, including a realistic estimate of the magnitude of effect of enhanced risk factor management in planning a future trial. A summary of the study design is provided in figure 1. Recruitment commenced in November 2015, was completed in July 2017 and final follow-up data collection will be in July 2018. The study has been registered on 16 April 2015: International Standard Randomised Controlled Trial Number 42688361.

**Figure 1 F1:**
[figure not shown]
Summary of the study design depicting the flow of participants through the study. Steps detailed include the identification and recruitment of participants, allocation and randomisation into the study arms based on Montreal Cognitive Assessment (MoCA) score, and the timing of intervention and follow-up visits. GP, general practitioner; TIA, transient ischaemic attack.

### Trial participants

All adult patients with confirmed stroke (first/recurrent) or TIA, identified within 8 weeks of diagnosis will be considered for the trial.

#### Inclusion criteria

Participant is willing and able to give informed consent for participation.Male or female, aged 18 years or above.Diagnosed clinically and radiologically with stroke (infarct or haemorrhage) or TIA.

#### Exclusion criteria

The participant may not enter the trial if ANY of the following apply:Established dementia.Life expectancy <1 year.Comorbidities that adversely affect their ability to accurately complete the MoCA.Patients who do not wish to know about their cognition.

### Identification of participants

Eligible patients will be given a detailed Patient Information Sheet (PIS) and Consent Form for consideration. After 24 hours the study team will contact the patient again and those who agree to participate will provide written informed consent and undergo a simple and validated cognitive screening test (MoCA), unless this has already been carried out by the clinical team as part of their routine care, whereupon that score can be used for study purposes. If a MoCA has been administered by the TIA clinic team the patient will be given a PIS in clinic and be followed up by phone to discuss entry into the study. Patients who have previously attended stroke services may be screened retrospectively from the Capture TIA/Stroke hospital database and followed up by phone. Those who have a MoCA score ≥26 and who verbally consent to be contacted about the study are sent a study summary sheet, a study invitation letter and consent form. If they wish to participate, the completed consent form will be returned and countersigned by a delegated member of the study team. Those who do not have a MoCA score following their stroke or TIA are invited for an appointment to give consent to take part in the study and carry out the MoCA. The patient will be enrolled into the appropriate arm of the study depending on the MoCA score.

